### Interventions

Patients will be randomized in a 1:1 ratio to receive either strategy A or strategy B. Patients randomized to strategy A will receive first line treatment with letrozole 2.5 mg once daily or anastrozole 1 mg once daily continuously in combination with either palbociclib 125 mg once daily or ribociclib 600 mg once daily on day 1–21 of every 28-day cycle. Second-line treatment will consist of fulvestrant 500 mg on day 1, day 15 and day 29 of the first month and monthly thereafter. Patients randomized to strategy B will receive letrozole 2.5 mg once daily or anastrozole 1 mg once daily continuously as first-line treatment. Second-line treatment will consist of fulvestrant 500 mg on day 1, day 15 and day 29 of the first month and monthly thereafter in combination with palbociclib 125 mg once daily on day 1–21 of every 28-day cycle. The proposed study design will be amended upon reimbursement to allow ribociclib also in strategy B and abemaciclib as third alternative CDK4/6 inhibitor. Patients will be stratified by site of disease (visceral versus non-visceral), prior endocrine treatment in (neo) adjuvant setting (yes versus no), hospital, and type of CDK4/6 inhibitor. All pre- and perimenopausal women will also receive ovarian ablation or suppression. Patients will continue to receive the assigned study medication until objective disease progression, symptomatic deterioration, or unacceptable toxicity (at the discretion of the treating physician), death, or withdrawal of consent, whichever occurs first. Patients will be screened at baseline for eligibility, and after signing informed consent, baseline measurements will be obtained. Subsequently, patients will be followed up according to their treatment group. Patients randomized to strategy A will undergo laboratory evaluation after 2, 4, 6, and 8 weeks and monthly thereafter. Patients randomized to strategy B will undergo laboratory evaluation three-monthly during first-line treatment. During second-line treatment, the follow-up schedule for patients in group A will be identical to that of patients in group B during first-line treatment and vice versa. In both treatment arms, response assessment and safety evaluation will be performed every three months by means of imaging, laboratory evaluation, evaluation of ECOG performance status, physical examination, and recording of adverse events and concomitant medication. Questionnaires regarding QoL and cost-effectiveness will be administered at several prespecified time points in the study. A table with all study-related activities can be found in Additional file 1.

### Dose modifications

Every effort should be made to administer study treatment on the planned dose and schedule. However, in the event of significant treatment-related toxicity, administration of CDK4/6 inhibitors may need to be adjusted. Dose adjustment is not permitted for non-steroidal AIs, fulvestrant or LHRH agonists. Depending on the nature of the toxicity observed, treatment interruption of CDK4/6 inhibitors may be required. Treatment with letrozole/anastrozole or fulvestrant will continue as pre-planned. For more information about dose modifications, see Additional file 2.

### Concomitant treatment

Standard therapies for pre-existing medical conditions, medical and/or surgical complications, and palliation are allowed during study participation. Palliative radiotherapy is allowed during the study, although it is recommended to initiate radiotherapy before study initiation if possible. Caution is advised on theoretical grounds for any surgical procedures during the study. The appropriate interval of time between surgery and CDK4/6 inhibitors required to minimize the risk of impaired wound healing and bleeding has not been determined. Medications not allowed during study participation include other anticancer agents, strong CYP3A4 inhibitors or inducers, hormone replacement therapy and hormonal contraception.

### Statistics: Sample size and power calculations

The primary outcome for this study is PFS2, defined as time from randomization to second objective progression. The threshold for a clinically relevant difference in PFS2 is set according to the European Society for Medical Oncology - Magnitude of Clinical Benefit Scale (ESMO-MCBS) [20]. The maximal preliminary score for efficacy based on PFS is 3 out of 4, with a higher score indicating more clinical benefit (see Table 1). The preliminary scores can be upgraded or downgraded depending on data on toxicity and quality of life to achieve the final score.

**Table 1 Tab1:** preliminary magnitude of clinical benefit grade based on PFS

Grade 3	HR ≤0.65 and gain ≥3 months
Grade 2	HR ≤0.65 but gain < 3 months
Grade 1	HR > 0.65

*PFS* progression-free survival, *HR* hazard ratio (thresholds refer to the lower extreme of the 95% confidence interval)

Based on the PALOMA-studies, we estimated strategy A to show a median PFS2 of 31 months and strategy B to show a median PFS2 of 28 months, with a corresponding hazard ratio of 0.85. For strategy A to be preferable according to ESMO-MCBS, a statistically significant difference in PFS of at least three months and a lower limit of the 95% confidence interval ≤ 0.65 for the corresponding hazard ratio is required. In the power calculation we implemented these minimum requirements by multiplying the estimated hazards in the palbociclib + letrozole group (PALOMA-2) and in the palbociclib + fulvestrant group (PALOMA-3) by 0.88 while multiplying the estimated hazards in the letrozole single agent group (PALOMA-2) and fulvestrant single agent group (PALOMA-3) by 1/0.88. This modification of the actual hazards yields expected median PFS2 times of 32.6 and 27.4 months in the strategy A and strategy B, respectively.

Based on 10,000 simulated trials with the modified hazards we conclude that inclusion of 500 patients per arm in a period of 42 months and an additional 18 months follow-up will yield an expected number of 574 events and 89% power to show that strategy A has statistically significant superior PFS2 in a log-rank test at the two-sided 95% confidence level. The corresponding hazard ratio for strategy A: strategy B is 0.765 (95% CI 0.648–0.902) and the probability of meeting the above-mentioned ESMO-MCBS criteria is 52%. If the study fails to detect superiority, non-inferiority will be tested next. According to the closed test principle, hierarchical testing of superiority and non-inferiority does not affect sample size or power of the analyses.

### Statistics: Analysis

#### Efficacy

The difference in PFS2 (primary endpoint) will be estimated using the intention-to-treat (ITT) population in a Cox proportional hazards model accounting for all stratification factors. An adjusted hazard ratio with a symmetric 1-α confidence interval will be produced.

Secondary objectives include comparisons of OS, ORR, QoL, safety and tolerability and cost-effectiveness. A stratified log-rank test (using the same stratification factors as for the PFS analysis) will be used to compare OS between the treatment strategies. The ORR on each randomized treatment strategy will be estimated by dividing the number of patients with objective response (either complete response (CR) or partial response (PR) according to RECIST 1.1) by the number of patients randomized to the respective treatment strategy (“response rate”). A 95% CI for the response rates will be provided. Response rate comparisons between the two treatment strategies as randomized will be assessed using Cochran-Mantel-Haenszel (CMH) test with the same stratification factors as for the PFS analysis. Analyses of ORR will be performed on the ITT population. Health related QoL will be analyzed using patient reported outcomes of the disease specific FACT-B and generic EQ-5D-5 L questionnaires [21, 22] (https://euroqol.org/eq-5d-instruments/eq-5d-5l-about/). The FACT-B and EQ-5D scoring guidelines will be used to compute FACT module specific scores, overall FACT-B quality of life scores, and EQ-5D utility scores. The cost and outcomes of both arms will be assessed by Mann Whitney test. Cost-effectiveness will be determined by comparing costs and effects of both treatment strategies by means of the Institute for Medical Technology Assessment Resource Use Questionnaire Borstkanker (iMTA-RUQ-B). This questionnaire was developed by iMTA by combining questions from the iMTA Productivity Cost Questionnaire (iPCQ), the iMTA Medical Consumption Questionnaire (iMCQ) and the iMTA Valuation of Informal Care Questionnaire (iVICQ) (https://www.imta.nl/questionnaires/) [23]. Quality adjusted life years (QALY) will be computed by multiplying life-years with the observed utility scores during those life years. As a societal perspective will be taken into account all relevant direct and indirect costs will be measured. In this respect, the friction cost method will be used for estimating the societal costs of productivity losses.

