### Legislation and logistics

The SONIA study was approved by the accredited Medical Ethics Committee of the Netherlands Cancer Institute – Antoni van Leeuwenhoek (METC AVL) on September 29th, 2017. The study will be conducted in accordance with legal and regulatory requirements, as well as the general principles set forth in the International Ethical Guidelines for Biomedical Research Involving Human Subjects, Guidelines for good Clinical Practice (GCP), and the Declaration of Helsinki. A total of 74 hospitals in the Netherlands will participate. Patients will be informed about the study and asked to participate by their treating physician.

A centralized internet/telephone registration system (ALEA) is used for randomization. All data will be recorded by qualified data managers in an electronic case report form (eCRF), which is managed by “Borstkanker Onderzoekgroep” (BOOG), the sponsor of this study. On site monitoring will take place conform the guideline of the “Nederlandse Federatie van Universitaire Medisch Centra” (NFU) called “Kwaliteitsborging van mensgebonden onderzoek 2012” by the appointed monitor.

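### Hospital (74 sites) is carried from the randomisation into the OS and ORR analysis strata, and possibly into the primary model, at an information cost the power calculation does not include

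*Protocol article*

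**What the plan says.** The Interventions section of the protocol article lists four randomisation factors: "Patients will be stratified by site of disease (visceral versus non-visceral"), then "prior endocrine treatment in (neo) adjuvant setting (yes versus no), hospital, and type of CDK4/6 inhibitor". Two inhibitors are in use, and an amendment to add a third is foreseen. Under Legislation and logistics: "A total of 74 hospitals in the Netherlands will participate".

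The Efficacy section estimates the PFS2 difference "in a Cox proportional hazards model accounting for all stratification factors", and adds: "An adjusted hazard ratio with a symmetric 1-α confidence interval will be produced". For OS: "A stratified log-rank test (using the same stratification factors as for the PFS analysis) will be used to compare OS". For ORR it names the "Cochran-Mantel-Haenszel (CMH) test with the same stratification factors as for the PFS analysis". Hospital is not exempted anywhere, and no pooling of small hospitals or sparse cells is described.

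The sample size section gives 500 patients per arm, 574 expected PFS2 events, a hazard ratio of 0.765 and 89% power for a two-sided log-rank test. It mentions no stratification.

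**The concern.** A stratified log-rank or CMH test compares the arms only within a cell. With fewer than two patients per possible cell, many patients have nobody in the other arm to be compared with, and their data drop out of the test. For OS and ORR the text fixes this: both tests take the factors of the PFS analysis, and that analysis takes all of them. An analysis plan that followed the article would inherit the problem.

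For the primary endpoint the wording leaves open whether the factors enter as strata or as covariates. The two readings differ greatly in cost, and neither is the test for which the 89% was computed. What is at stake is precision and power. Sparse strata do not inflate the type I error.

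**Working it through.** **1. The plan's own power.** Schoenfeld: power = Φ(|ln HR|·√d/2 − 1.96). With HR 0.765, |ln HR| = 0.2679. With d = 574: 0.2679 × 23.96/2 = 3.209, and Φ(1.249) = 89.4%. The confidence interval from SE = 2/√574 = 0.0835 is 0.650-0.901 (stated 0.648-0.902). The stated figures therefore reproduce for an unstratified test.

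**2. Cells.** 74 × 2 × 2 × 2 = 592 possible cells, or 1000/592 = 1.7 patients per cell. With three inhibitors, 74 × 2 × 2 × 3 = 888, or 1.1 per cell. These are possible cells. In simulation about 270-480 of the 592 were occupied.

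**3. CMH loss in closed form.** A cell with n patients, of whom a and b are in the two arms and r respond, contributes a·b·r·(n−r)/[n²(n−1)]. This is zero if n = 1 or if one arm is empty. Under simple 1:1 randomisation with response rate p, its expectation under no treatment effect is (n−1)p(1−p)/4. Summed over K occupied cells this is (N−K)p(1−p)/4, against (N−1)p(1−p)/4 without strata. The loss is therefore (K−1)/(N−1).

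- Equal hospitals and even splits of the other factors (assumed): K = 592 × [1 − (1 − 1/592)^1000] = 483, so the loss is 482/999 = 48%.
- Unequal hospitals and one inhibitor only: simulated K = 229, giving 228/999 = 23% (simulated 22.7%).
- Hospital removed: K = 8, giving 7/999 = 0.7%.

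**4. Log-rank loss.** By the same argument, an event with m patients still at risk in its cell carries (1 − 1/m)/4 instead of about 1/4. Since m shrinks as patients leave the risk set, the log-rank test loses more than CMH. In a cell of two patients, one per arm, the second event carries nothing.

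**5. Simulation.** 1000 patients, 74 hospitals, exponential PFS2 with HR 0.765, accrual over 42 months plus 18 months of follow-up (about 596 events), 120 trials per scenario. Assumed: 55% visceral disease, 50% prior endocrine treatment, 40% response rate, and equal to strongly unequal hospital sizes.

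| Scenario | Log-rank loss | CMH loss |
|---|---|---|
| Two inhibitors, simple randomisation or minimisation | 36-62% | 24-48% |
| Two inhibitors, blocks of two within each full cell | 26-43% | 11-21% |
| Three inhibitors (40/40/20) | 43-70% | 24-58% |
| One inhibitor dominant, or one per hospital | 22-44% | 6-28% |
| Hospital removed (8 cells) | about 1% | under 1% |

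**6. What this would mean for PFS2**, putting 574 × (1 − loss) into step 1:

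| Loss | Effective events | Power |
|---|---|---|
| 0% | 574 | 89.4% |
| 11% | 511 | 85.7% |
| 35% | 373 | 73.5% |
| 55% | 258 | 57.6% |

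The 11% row is the covariate reading. With 73 hospital indicators and equal hospital sizes, the SE of the log hazard ratio rose from 0.082 to 0.087, the mean information loss was 10.9%, and simulated power was 85-87% against 89-90% unadjusted. With unequal sizes some fits did not converge. The 35% and 55% rows apply only if the Cox model is stratified on the full cross-classification.

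**The case against.** The primary model speaks of accounting for factors and of an adjusted hazard ratio, which fits covariates at least as well as strata. On that reading power falls only from 89% to about 86%. The choice between strata and covariates, and the pooling of small centres, are often left to an analysis plan, which is not shown here. This stands: the large losses cannot be attached to the primary analysis as written. It does not help OS and ORR, which the text expressly stratifies on the same factors.

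The size of the loss rests on inputs the article does not give. This also stands, and is why the loss is given as a range. No OS event count is stated either, so the log-rank losses come from PFS2 event rates. With fewer deaths the loss would probably move towards the CMH figures, but this was not computed.

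Several stronger readings are tempting, and the document does not support them:

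- **That every analysis is affected.** It is not: "The cost and outcomes of both arms will be assessed by Mann Whitney test", with no stratification stated.
- **That OS and ORR fall short of a planned power.** Power is stated for PFS2 only.
- **That the wider interval makes the ESMO-MCBS limit of 0.65 easy to meet.** Significance and a gain of at least three months are also required. Take an observed HR of 0.80. At full information (574/4 = 143.5) the interval is 0.679-0.942, which misses the limit. At 40% loss (86.1) it is 0.648-0.988, which meets it. At information 92 it is 0.652-0.981, which misses the limit. At 62 it is 0.624-1.026, which is not significant. The effect occurs only in a narrow window and only under full stratification.
- **That inhibitor type is collinear with arm** because strategy B currently allows palbociclib only. This would need the factor to be coded as received. A randomisation factor must be known before allocation, and nothing in the text says otherwise.

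**Conclusion.** The point holds for OS and ORR. As written, both tests are stratified on up to 592 possible cells (888 with a third inhibitor) for 1000 patients. They would lose roughly 22-70% of the information (log-rank) and 6-58% (CMH) over the hospital sizes, inhibitor shares and allocation methods assumed here. With simple randomisation or minimisation and two inhibitors, the ranges are 36-62% and 24-48%.

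For PFS2 the defect is an ambiguity. The covariate reading costs about 11% of the information, with power about 86% (equal hospital sizes assumed). Full stratification would leave about 74-58% at losses of 35-55%. On neither reading does the planned analysis match the unstratified log-rank test behind the 89%. A reader might infer that the primary analysis has certainly lost a third to a half of its information. The text does not establish that.

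**What to change.** In the Efficacy section or the analysis plan:

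- Keep hospital as a randomisation factor only.
- Use site of disease, prior endocrine treatment and inhibitor type as declared before randomisation in the PFS2 Cox model, the OS log-rank test and the ORR CMH test.
- State whether these factors enter the Cox model as strata or as covariates.
- If hospital is of interest, add it as a random effect in a sensitivity analysis.

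This takes a few lines of text and no extra data, and should be settled before unblinding. It brings the loss in the stratified tests down to about 1%. In the 8-cell simulation, power for PFS2 was 91%, against 92% unstratified. The cost is that the main tests no longer condition on differences between hospitals.

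### Costs and QALYs: the only between-arm method named is a rank test, which does not address the mean differences that a cost-effectiveness comparison needs

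*Protocol article*

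**What the plan says.** Cost-effectiveness is a secondary objective: "Secondary objectives include comparisons of OS, ORR, QoL, safety and tolerability and cost-effectiveness". For its analysis, Statistics: Analysis, Efficacy makes four statements.

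- On the test: "The cost and outcomes of both arms will be assessed by Mann Whitney test".
- On how cost-effectiveness is reached: "Cost-effectiveness will be determined by comparing costs and effects of both treatment strategies by means of the Institute for Medical Technology Assessment Resource Use Questionnaire" (the name of the instrument continues). This is a data-collection instrument, not an estimator.
- On effects: "Quality adjusted life years (QALY) will be computed by multiplying life-years with the observed utility scores during those life years".
- On perspective: "As a societal perspective will be taken into account all relevant direct and indirect costs will be measured", with productivity losses valued by the friction cost method.

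The same section gives OS a stratified log-rank test and ORR a Cochran-Mantel-Haenszel test. For costs and QALYs the Mann-Whitney test is the only between-arm method named.

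**The concern.** A societal comparison of cost per QALY is a comparison of arithmetic means, because mean cost times number of patients is total cost, and the same holds for QALYs. A Mann-Whitney test addresses the probability that a patient in one arm has a higher value than a patient in the other. The shift estimate usually attached to it is the median of pairwise differences, which is not the difference in means either. Rank and mean comparisons agree when one distribution is a simple shift of the other.

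A pure shift is unlikely here. Under Interventions, every strategy A patient is assigned the CDK4/6 inhibitor from the start, while a strategy B patient reaches it only on second-line treatment. The Background puts average use at about 25 months in first line and 9 to 16 months in later lines. Time to start and duration both differ, so the spread and skewness of cost may differ as well as its level.

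At stake is the statistical basis of the cost-effectiveness result: a p-value that may point away from the mean difference, and no interval for the quantity that enters the ratio.

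**Working it through.** **The plan's own figure.** The article states no power for costs or QALYs. Its one power figure is for PFS2: "an expected number of 574 events and 89% power" in a "log-rank test at the two-sided 95% confidence level", at a hazard ratio of 0.765. The Schoenfeld formula gives √574/2 × |ln 0.765| − 1.96 = 11.98 × 0.268 − 1.96 = 1.25, and Φ(1.25) = 89.4%. The stated 89% is reproduced, and nothing below changes it.

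**Inputs.** From the article: n = 500 per arm, two-sided 5%. Assumed, because the article has no cost data: lognormal costs, log-SD 0.6 in one arm and 0.8 in the other, scale 50 in arbitrary units.

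**Case 1: equal medians, unequal means.**
- Means: 50·exp(0.6²/2) = 59.9 and 50·exp(0.8²/2) = 68.9; ratio 1.15.
- The probability that one arm exceeds the other is exactly 0.5, so Mann-Whitney has nothing to detect.
- Simulation of 2,000 trials: Mann-Whitney rejects in 6%, a Welch test of means in 79%. A check with 10,000 trials gave 5% and 77%; another run gave 5% and 75%.
- With log-SD 0.6 and 1.0 the means are 59.9 and 82.4 (38% apart): about 5% against nearly 100%.

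**Case 2: equal means, unequal spread.**
- With both means at 50, the medians are 50·exp(−0.18) = 41.8 and 50·exp(−0.32) = 36.3.
- The log-medians differ by 0.32 − 0.18 = 0.14. The probability that the more spread arm exceeds the other is Φ(−0.14/√(0.36 + 0.64)) = Φ(−0.14) = 0.444.
- The null standard error of that probability is √[(2n+1)/(12n²)] = √(1001/3,000,000) = 0.0183. The distance is (0.5 − 0.444)/0.0183 ≈ 3.05, so approximate power is Φ(3.05 − 1.96) = 86%.
- Simulation: Mann-Whitney rejects in 86%, the comparison of means in about 5%.

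**Case 3: the article's own durations of use.** Follow-up is fixed by "500 patients per arm in a period of 42 months and an additional 18 months follow-up", that is 18 to 42 + 18 = 60 months. I assumed exponential durations of use with mean 25 months in A and 9 or 16 months in B, with B starting after an exponential first line of median 14.5 months (the control median that the Background quotes for first-line letrozole). In 1,000 trials both tests rejected every time. Mean observed months of use were 19.1 in A against 6.3 or 9.5 in B. The mean differences, about 12.8 and 9.5 months, are clearly unlike, yet the rank test returns the same verdict for both. Detection is not lost; the size of the difference is.

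**Why the replacement should allow for censoring.** QALYs build on life-years, and potential follow-up runs from 18 to 60 months. The article gives no OS assumption. With exponential OS and assumed medians of 30 to 60 months, 42% to 64% of patients are alive at the cut-off. Mean observed life-time is then 25.1 to 30.9 months against a 60-month restricted mean of 32.5 to 43.3, which is 23% to 29% lower. An ordinary Mann-Whitney test on observed totals has no term for this.

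**The case against.** The strongest reply is that the article never says the rank test decides cost-effectiveness. The sentence after it says that costs and effects will be compared, and a rank test on skewed costs can stand beside a comparison of means as description. The term outcomes is also undefined. The sentence directly follows the scoring of FACT-B and EQ-5D, so it may mean those scores, for which a rank test is a reasonable description. This part stands and limits the point to costs and QALYs. It does not remove the point: costs are named explicitly, and the only further method given for comparing costs and effects is a questionnaire.

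Three stronger readings are tempting and are not supported.

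- A reader might infer that the plan ignores censoring, or counts a living patient's follow-up as her whole life. The article gives the usual definition of a QALY and is silent on horizon and censoring; a full protocol or economic analysis plan may settle both.
- A reader might take the patients without a PFS2 event, implied by 574 events in 1,000, as the share with incomplete QALYs. QALYs are incomplete for patients alive at the cut-off, and PFS2 events do not give that share.
- A reader might model a fixed fraction of strategy B at zero drug cost, by adding the 15% in Compliance to those still on first line. The 15% is a threshold for stopping inclusion, not an expected rate, and patients still on first line at the cut-off are not final zeros. Such a model also covers drug cost alone. When an assumed background cost is added, its Mann-Whitney rejection rate at equal means falls to between about 10% and 92%, depending on the size and shape of that cost.

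**Conclusion.** The point holds as a mismatch between the method stated and the quantity needed. The Mann-Whitney test does not test or estimate differences in mean cost and mean QALYs, and it can err in both directions: about 5% rejection against 75% to 79% for a comparison of means when means differ by 15% at equal medians, and about 86% against 5% when means are equal and spread differs. These rates rest on assumed lognormal costs and show the mechanism; they are not forecasts for this trial. With the durations of use in the Background, both tests would find a difference in drug use, so the practical loss is the estimate and its interval rather than detection. The matter is confined to a secondary objective. It loses no data, and it leaves the PFS2 analysis, sample size and power as they are.

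**What to change.** For costs and QALYs, replace the Mann-Whitney sentence with between-arm differences in arithmetic mean cost and mean QALYs over a stated horizon, with non-parametric bootstrap 95% intervals. Combine the two as an incremental cost-effectiveness ratio or net benefit, showing joint uncertainty. Because follow-up is staggered from 18 to 60 months, use an estimator that allows for censoring, such as inverse-probability-of-censoring weighting; if a separate economic plan already does so, refer to it. Define which outcomes the Mann-Whitney test covers. It may stay as a descriptive comparison of questionnaire scores. The cost is a little more analysis work, with no new data and no change in sample size.

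### The only between-arm method the article names alongside the FACT-B and EQ-5D scores is a Mann Whitney test, which cannot adjust for baseline or model the repeated questionnaires

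*Protocol article*

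**What the plan says.** All of this comes from the protocol article.

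- *Statistics: Analysis, Efficacy* makes QoL a secondary comparison: "Secondary objectives include comparisons of OS, ORR, QoL, safety and tolerability and cost-effectiveness".
- The same section names the instruments: "Health related QoL will be analyzed using patient reported outcomes of the disease specific FACT-B and generic EQ-5D-5 L questionnaires". The scoring guidelines will be used to "compute FACT module specific scores, overall FACT-B quality of life scores, and EQ-5D utility scores".
- The next sentence is: "The cost and outcomes of both arms will be assessed by Mann Whitney test". The text then turns to cost-effectiveness. No other between-arm test or model for QoL appears.
- In the same section, PFS2 gets a Cox model with all stratification factors, overall survival a stratified log-rank test, and response rate a stratified Cochran-Mantel-Haenszel test.
- *Interventions* gives the data structure: "Questionnaires regarding QoL and cost-effectiveness will be administered at several prespecified time points in the study". On baseline it says that "after signing informed consent, baseline measurements will be obtained", without naming a questionnaire among them.
- *Statistics: Sample size and power calculations* gives QoL a role in the ESMO-MCBS grade: "The preliminary scores can be upgraded or downgraded depending on data on toxicity and quality of life to achieve the final score".

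**The concern.** This is a stated method, not a detail left to the analysis plan, and it fits the data badly. A Mann Whitney test compares one number per patient between two groups. It has no place for a baseline covariate, for the four stratification factors, or for the correlation between visits. (Stratified rank tests exist, but none is named.) QoL would then be compared with less adjustment than the other efficacy endpoints in the same section.

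Two things are at stake. The first is precision: baseline QoL usually predicts later QoL, and leaving it out wastes information. The second is validity: a test of returned forms can show a difference that is not there if sicker patients stop answering and do so at different rates in the two arms. Both matter in a trial whose Background argues that first-line use brings longer exposure and more toxicity without clear QoL benefit, and where QoL may move the benefit grade.

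**Working it through.** **The plan's own figure.** The only power stated is for PFS2. With 574 events and a hazard ratio of 0.765, z = |ln 0.765| × √574 / 2 − 1.96 = 0.268 × 11.98 − 1.96 = 1.25, so power is 89.4%, against 89% stated. It reproduces but does not bear on QoL.

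**Inputs for QoL.** The article gives 500 patients per arm and 1:1 allocation. It gives no QoL effect, standard deviation, correlation or completion rate. Those below are assumptions.

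**Precision, one follow-up visit, raw scores.** The efficiency of Mann Whitney relative to a t-test on normal data is 0.955. Adjusting for a baseline score with correlation r multiplies the residual variance by 1 − r². The ratio of patients needed (Mann Whitney to adjusted analysis) is 1 / [0.955 × (1 − r²)]. Power is shown for an assumed difference of 0.18 SD:

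| r | Patient ratio | Mann Whitney power | Adjusted power |
|---|---|---|---|
| 0.3 | 1 / (0.955 × 0.91) = 1.15 | 79% | 85% |
| 0.5 | 1 / (0.955 × 0.75) = 1.40 | 79% | 91% |
| 0.7 | 1 / (0.955 × 0.51) = 2.05 | 79% | 98% |

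With 350 per arm answering, the figures are 64% against 70%, 79% and 92%. Most of the gain comes from the baseline: without the 0.955 factor the ratios at r = 0.5 and 0.7 are still 1 / 0.75 = 1.33 and 1 / 0.51 = 1.96.

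**Repeated visits.** The variance of a baseline-adjusted mean of k visits with common correlation r is (1 + (k − 1)r)/k − r². Going from one visit to four reduces it from 0.75 to 0.375 (r = 0.5) and from 0.51 to 0.285 (r = 0.7).

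**Change scores.** If the test were run on change from baseline, with equal variances, the variance is 2(1 − r) and the ratio becomes 2 / [0.955 × (1 + r)]. That is 2 / 1.4325 = 1.40 at r = 0.5 and 2 / 1.6235 = 1.23 at r = 0.7.

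**Bias.** This was simulated with no true effect, 500 per arm, r = 0.6, one follow-up form and 2,000 runs per setting. The chance of a missing form rises as the score falls. Rejection at the 5% level:

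| Dropout A / B | Driven by | Mann Whitney | Baseline-adjusted |
|---|---|---|---|
| 30% / 30% | baseline score | 5% | 6% |
| 30% / 30% | unseen current score | 6% | 6% |
| 20% / 30% | baseline score | 9% | 4% |
| 20% / 40% | baseline score | 24% | 6% |
| 20% / 30% | unseen current score | 22% | 16% |
| 20% / 40% | unseen current score | 61% | 46% |

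So bias needs dropout that is both related to health and unequal between arms. Adjustment removes it when dropout depends on observed scores, but not when it depends on unseen ones.

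**The case against.** **The sentence may not be about QoL.** It speaks of cost first and leads into cost-effectiveness, so *outcomes* could mean health-economic outcomes. This ambiguity is real. The placement straight after the QoL scores favours the QoL reading. On the other reading, QoL has no comparison method in the article and the sentence still needs clarifying.

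**The tested quantity is not given.** A reader might infer that the baseline and earlier forms are simply discarded. The article does not say so: the test could use change from baseline or a per-patient average. Such a summary would recover part of the information, but the test would still omit the stratification factors and leave missing forms unresolved.

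**Unequal dropout is not shown.** A reader might infer that the comparison is biased because, with exponential times and the quoted first-line medians of 24.8 and 14.5 months, 51% of A and 32% of B are still in first line at month 24. That is progression, not questionnaire completion, and nothing says forms stop at first progression; both arms continue into second-line study treatment. On the article's PFS2 medians the same calculation gives 59% v 55% (31 and 28 months) or 60% v 54% (32.6 and 27.4), a gap of 3 to 6 points. The documents support only that bias is possible.

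**The remedy is not immune.** The simulation confirms this for unseen scores, and a mixed model treats scores after death as merely missing. Hence the sensitivity analysis below.

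**Other stronger readings.** Multiplicity across FACT modules and visits is detail that an article may leave to the analysis plan. Nor should a QoL contrast alone govern the ESMO-MCBS grade, since the sample size section names toxicity as well.

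**Conclusion.** The point stands as a choice of method that should be improved for a secondary endpoint. The Mann Whitney test, as named and apparently meant to cover QoL, cannot use the baseline score, the stratification factors or the repeated structure of the data. If raw follow-up scores are tested, the loss is equivalent to 1.40- to 2.05-fold more patients. That range rests on assumed baseline correlations of 0.5 to 0.7 and roughly normal scores; a skewed score, such as a utility, could change the 0.955 factor. Bias is a conditional risk that cannot be sized from the article. PFS2 and its sample size are not affected. If the full protocol or analysis plan already holds a longitudinal QoL model, the article's sentence needs only to be reconciled with it.

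**What to change.** For QoL, replace the Mann Whitney sentence with text along these lines: *FACT-B total score and EQ-5D utility are analysed in the intention-to-treat population by a linear mixed model for repeated measures from randomisation, with baseline score, arm, visit, arm-by-visit interaction and the stratification factors (hospital as a random effect or pooled). The main QoL contrast is the between-arm difference in FACT-B total, with its 95% confidence interval. A sensitivity analysis addresses missing forms and death.* The analysis plan should fix the visit or window for the contrast. Keep Mann Whitney, if wanted, for costs only, and say so.

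The cost is one paragraph. No new data are needed if a baseline questionnaire is among the prespecified time points, which the article makes likely but does not state. The small downside is that the model assumes missingness depends on observed data, so bias remains if it depends on unseen scores; the sensitivity analysis is there to show how much that could matter.
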